## Abstract

**Introduction:**

Several biologic agents have emerged as novel therapeutic options for patients with generalized myasthenia gravis (gMG); however, no clinical studies have yet explored the efficacy and safety of sequential biologic therapy in gMG.

**Methods and analysis:**

This multicenter, open-label, randomized controlled, exploratory clinical trial plans to enroll 60 patients with acetylcholine receptor antibody-positive gMG, randomized in a 1:1:1 ratio to receive one of the following treatment regimens: (1) E + 1w+T: efgartigimod 10 mg/kg weekly for 4 weeks, followed by telitacicept 240 mg weekly starting 1 week after the last efgartigimod dose, continued for 25 weeks; (2) E + 2w+T: efgartigimod as above, followed by telitacicept 240 mg weekly starting 2 weeks after the last efgartigimod dose, continued for 24 weeks; or (3) T only: telitacicept monotherapy for 30 weeks. The primary endpoint is the change in the Quantitative Myasthenia Gravis (QMG) score from baseline to week 30. Secondary endpoints include changes in the Myasthenia Gravis Activities of Daily Living (MG-ADL) score from baseline, proportion of patients achieving minimal manifestation status (MMS), changes in dosages of corticosteroid and other immunosuppressant, rates of MG relapse/acute exacerbation and MG crisis, and safety outcomes. The pharmacokinetics/pharmacodynamics (PK/PD) of telitacicept will also be assessed. Recruitment is currently ongoing, but no participants have been enrolled as of yet.

**Ethics and dissemination:**

The study has been approved by the Ethics Committee in Clinical Research of the First Affiliated Hospital of Wenzhou Medical University. Results of the study will be disseminated to the relevant scientific, clinical and patient communities on trial closure.

Trial registration number: The study was registered at ClinicalTrials.gov (NCT06827587).

## Introduction

1

Myasthenia gravis (MG) is an autoimmune neuromuscular disorder mediated by autoantibodies, characterized primarily by localized or generalized muscle weakness and fatigability (1, 2). A recent systematic review estimated the global prevalence of MG to be approximately 173.3 per million, with an annual incidence of 15.7 per million (3). In China, the age- and sex-adjusted annual incidence of MG is approximately 0.68 per 100,000, with an in-hospital mortality rate of 1.469% (4). Approximately 85% of patients develop generalized myasthenia gravis (gMG), which predominantly affects the proximal muscles of the limbs and trunk (2, 4). Myasthenic crisis occurs in 15-20% of patients with gMG, often leading to respiratory failure and bulbar palsy, and requiring intensive care (1, 5).

The pathogenesis of MG is primarily mediated by immunoglobulin G (IgG) autoantibodies targeting postsynaptic membrane receptors, impairing neuromuscular transmission (5). Acetylcholine receptor antibodies (AChR-Ab) are the most prevalent, detected in about 80% of MG cases (1, 5). A smaller proportion of patients have antibodies against muscle-specific tyrosine kinase (MuSK) or low-density lipoprotein receptor-related protein 4 (LRP4). Standard treatment includes cholinesterase inhibitors, corticosteroids, and conventional immunosuppressants, along with intravenous immunoglobulin (IVIg) or plasma exchange (PLEX) for acute exacerbations (2, 6, 7). However, current therapies are limited by delayed onset of action, broad adverse effect profiles, unstable symptom control during corticosteroid tapering, and high relapse rates (8). Many gMG patients fail to achieve minimal manifestation status (MMS) promptly and persistently or endure chronic treatment-related morbidity. Thus, there remains a critical unmet need for safe, effective, and durable therapies that provide early disease control and reduce long-term immunosuppressant exposure.

In recent years, novel biologic agents have significantly expanded the treatment landscape for gMG. These include complement inhibitors (e.g., eculizumab), neonatal Fc receptor (FcRn) antagonists (e.g., efgartigimod), and B-cell-targeted therapies (e.g., telitacicept) (5). Eculizumab was approved in China in 2023 for anti-AChR-Ab-positive refractory gMG, though symptom worsening upon discontinuation has been reported (9). Efgartigimod, approved in China in September 2023, rapidly alleviates symptoms by promoting IgG degradation through FcRn inhibition (10, 11). Both intravenous and subcutaneous formulations have now been approved by the U.S. Food and Drug Administration, the European Medicines Agency, and more recently by Chinese regulatory authorities for the treatment of gMG. Yet its clinical benefit may be short-lived, with symptom rebound linked to anti-AChR antibody overshoot and a relatively short half-life (4.89 days) (12–14). Real-world studies indicate that scores such as Quantitative Myasthenia Gravis (QMG) and Myasthenia Gravis Activities of Daily Living (MG-ADL) begin to rebound within 2–3 weeks of completing a 4-week cycle (10, 14). Because subsequent treatment cycles cannot begin until 7 weeks post-initiation, the need for a durable maintenance strategy after efgartigimod-induced remission is pressing. Telitacicept, a recombinant fusion protein targeting BLyS and APRIL, inhibits B-cell maturation and plasma cell differentiation, thereby reducing autoantibody production (15, 16). It is approved in China for systemic lupus erythematosus and has shown promising efficacy and tolerability in gMG. A multicenter phase 2 trial reported sustained QMG and MG-ADL improvements over 24 weeks (15). A 2024 retrospective study showed that 90.1% of patients with refractory gMG experienced sustained clinical benefit and corticosteroid dose reduction after 6 months of telitacicept therapy (17). Its subcutaneous route also facilitates long-term outpatient administration.

Mechanistically, efgartigimod and telitacicept act on complementary immunologic pathways. Efgartigimod provides rapid, downstream clearance of pathogenic IgG (10, 18), while telitacicept offers prolonged, upstream suppression of autoantibody production (16). Therefore, sequential use may enable both rapid symptom control and long-term disease stabilization. Furthermore, this biologic induction-maintenance model may facilitate early corticosteroid tapering and reduce reliance on long-term immunosuppression. In our previous case series, seven patients who responded poorly to conventional therapies demonstrated significant improvement in QMG and MG-ADL scores following treatment with telitacicept and efgartigimod, with no reported adverse events (19). These preliminary findings support the safety and feasibility of sequential biologic therapy. Nevertheless, one unresolved question is the optimal timing of telitacicept initiation after efgartigimod. As a human IgG Fc fusion protein, telitacicept could be prematurely catabolized by residual efgartigimod, potentially reducing its bioavailability. If administered too late, however, symptom rebound may occur before telitacicept becomes effective. Based on prior pharmacokinetic modeling and clinical experience, we decided to evaluate both 1-week and 2-week intervals between therapies.

To address this clinical gap, we propose a multicenter, open-label, randomized controlled trial comparing two sequential efgartigimod-telitacicept regimens versus telitacicept monotherapy in patients with AChR-Ab-positive gMG. This study will assess efficacy, safety, and pharmacokinetics/pharmacodynamics (PK/PD) parameters, with the aim of defining an optimal sequencing strategy. This approach could represent a novel treatment paradigm for patients with refractory gMG, offering a biologics-based induction-maintenance model to improve early disease control and reduce corticosteroid dependency.

## Methods and analysis

2

### Study design

2.1

This study is a multicenter, open-label, randomized controlled clinical trial which will be conducted at five centers, including the First Affiliated Hospital of Wenzhou Medical University. The study will adhere to Good Clinical Practice standards and the principles of the Declaration of Helsinki. The protocol has been approved by the Ethics Committee in Clinical Research of the First Affiliated Hospital of Wenzhou Medical University (KY2024-298) and has been registered at ClinicalTrials.gov (NCT06827587).

### Study subjects

2.2

The study will enroll patients aged 18–80 years with AChR-Ab-positive gMG, classified as Myasthenia Gravis Foundation of America (MGFA) Class II-IV [15]. Full eligibility criteria are provided in **Table 1**.

**Table 1 T1:** Inclusion and exclusion criteria.

Inclusion criteria
1. Patients must voluntarily sign the informed consent form.
2. Age between 18 and 80 years, inclusive, with no sex restrictions.
3. Diagnosis of MG according to the 2020 Chinese Guidelines for the Diagnosis and Treatment of MG, with serologically confirmed AChR-Ab positivity.
4. Classified as Myasthenia Gravis Foundation of America (MGFA) clinical class II–IV.
5. Patients with fluctuating MG symptoms before enrollment, defined as an MG-ADL score ≥6 or a Quantitative Myasthenia Gravis (QMG) score ≥8, persisting for more than 24 hours.
Exclusion criteria
1. Presence of other active autoimmune diseases, such as systemic lupus erythematosus, rheumatoid arthritis, or Sjögren’s syndrome.
2. Active infections, including herpes zoster, HIV, active tuberculosis, or active hepatitis.
3. Thymoma with a history of surgery within the past six months.
4. History of malignancies other than thymoma.
5. Severe hepatic or renal impairment, defined as ALT or AST >3×ULN, or an estimated glomerular filtration rate (GFR) <30 mL/min/1.73 m².
6. Serum IgG level ≤400 mg/dL.
7. Prior use of biologic agents within five times their elimination half-life, including: Telitacicept within two months prior to enrollment. Efgartigimod within one month prior to enrollment. Rituximab or other targeted biologic therapies within six months prior to enrollment.
8. Use of intravenous immunoglobulin (IVIG) or plasma exchange within two months before enrollment.
9. Receipt of any live vaccine within three months prior to enrollment or planned vaccination during the study period.
10. Pregnant or lactating women and those planning to conceive during the study period.
11. Known hypersensitivity to human-derived biologic products.
12. Participation in any clinical trial within 28 days before enrollment or within five times the elimination half-life of the investigational drug.
13. Other conditions deemed inappropriate for study participation by the investigator (e.g., severe psychiatric disorders).

### Randomization and intervention

2.3

Randomization will be conducted using a computer-generated random sequence, with all assignments managed through a central randomization system to ensure allocation concealment. Eligible participants will be randomly assigned in a 1:1:1 ratio to one of three groups, with 20 patients per group: E + 1w+T group: Efgartigimod followed by telitacicept with a 1-week interval; E + 2w+T group: Efgartigimod followed by telitacicept with a 2-week interval; T only group: Telitacicept monotherapy. All participants will receive biologic therapy in addition to standard-of-care treatments, which include acetylcholinesterase inhibitors, corticosteroids, and non-steroidal immunosuppressants such as tacrolimus. The study flowchart is shown in **Figure 1**.

**Figure 1 f1:**
[figure not shown]
Study flowchart. MG, myasthenia gravis.

E+1w+T group: Participants will receive efgartigimod induction therapy at 10 mg/kg, administered via intravenous infusion over 1 hour, once weekly for a total of 4 consecutive doses (Weeks 0–3). One week after completing induction therapy, telitacicept maintenance therapy will be initiated at a dose of 240 mg, administered subcutaneously once weekly from Week 4 for a total of 25 weeks. Participants will be followed until Week 30.

E+2w+T group: Participants will receive efgartigimod induction therapy at 10 mg/kg via intravenous infusion, once weekly for a total of 4 consecutive doses (Weeks 0–3), as in the E + 1w+T group. However, telitacicept maintenance therapy (240 mg, subcutaneously once weekly) will be initiated two weeks after completing induction therapy, starting from Week 5, and will continue for 24 weeks. Participants will be followed until Week 30.

T only group: Participants will not receive efgartigimod induction therapy. Instead, they will receive telitacicept 240 mg subcutaneously once weekly from Week 0 for a total of 30 weeks. Participants will be followed until Week 30.

From Week 8 to Week 30, if the patient reaches the Minimal Symptom Expression (MSE) criterion (MG-ADL ≤ 1) or experiences significant improvement in the Post-Intervention Status (PIS), or if the investigator deems dose reduction necessary, a reduction in the standard treatment is allowed. The recommended sequence for dose reduction is to first reduce or discontinue pyridostigmine bromide, followed by a reduction or discontinuation of non-steroidal immunosuppressive agents (e.g., tacrolimus, azathioprine, mycophenolate mofetil), and finally a reduction or discontinuation of corticosteroids. However, this order may be adapted at the discretion of the investigator based on the patient’s clinical condition, medication tolerance, and treatment response. To ensure stable disease control, a 2–4 week interval should be observed between the reduction or discontinuation of each class of medication. If disease exacerbation occurs during the study (MG-ADL increase≥2 points), but the patient does not reach a crisis state, an increase in the standard treatment or the use of a rescue regimen is permitted.

### Rescue treatment for MG exacerbation or crisis

2.4

In the event of a myasthenic crisis (V-type) during the study, investigational treatment will be immediately discontinued. The investigator will initiate appropriate rescue therapies, which may include, but are not limited to: 1) High-dose corticosteroids, such as methylprednisolone 1000 mg/day intravenously for 3 consecutive days, followed by a tapering regimen. Each infusion should be administered over 3–4 hours to reduce cardiac adverse effects; 2) IVIG at 400 mg/kg/day for 5 consecutive days; 3) PLEX, typically performed every other day during the first week (3 sessions), followed by weekly sessions depending on clinical response, for a total of 5–7 treatments. Each session may include replacement with approximately 1500 mL of fresh-frozen plasma and 500 mL of plasma substitute; 4) Supportive measures, including stabilization of vital signs, respiratory support, and symptomatic treatment for comorbid conditions as necessary, provided they do not interfere with efficacy evaluation.

For patients who experience moderate exacerbation (e.g., MG-ADL increase ≥2 points without meeting crisis criteria), the investigator may escalate standard therapy or initiate rescue treatment per clinical judgment. All adverse events and therapeutic interventions will be documented per protocol.

### Criteria for discontinuing

2.5

Patients have the right to withdraw from the study at any time for any reason. The investigator has the authority to terminate a patient’s participation under the following circumstances: pregnancy; receipt of rescue treatment; occurrence of adverse events that make the patient unsuitable for continued participation; significant laboratory abnormalities; serious violations of the study protocol; loss to follow-up; study termination due to management or other reasons; the investigator’s assessment that the patient is not benefiting from the study; or if continued participation poses unacceptable risks to the patient.

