### Endpoints

2.6

The primary endpoint is the change from baseline in the QMG score at Week 30 after randomization. Secondary endpoints include the assessment of the following variables at Weeks 4, 8, 12, 18, 24, and 30 after randomization: change from baseline in the MG-ADL score; the proportion of patients achieving minimal manifestation status (MMS) (defined as the absence of any functional limitations due to myasthenia, with certain weakness detected by a trained neurologist); the proportion of patients with a reduction of ≥2 points in the MG-ADL score from baseline; the proportion of patients with a reduction of ≥3 points in the QMG score from baseline; changes in the dose of corticosteroids and other immunosuppressive agents at Weeks 24 and 30; the proportion of patients who discontinue corticosteroids and other immunosuppressive agents at Weeks 24 and 30; the proportion of patients on prednisone (or equivalent corticosteroids) ≤5 mg/day at Weeks 24 and 30; the incidence of MG relapse/acute exacerbation and MG crisis at Week 30; and the incidence of AEs and SAEs.

The study will also analyze the PK/PD characteristics of telitacicept in different sequential treatment groups. Blood samples will be collected to measure PK-related indicators before the first administration of telitacicept (30 minutes prior), and at 6, 24, 48, and 72 hours, as well as at Week 1, 4, 8, 12, and 24 (before each dose). The PK parameters to be measured include blood drug concentration, clearance rate, volume of distribution, interindividual variability, and other relevant indicators. Immune globulins will be tested during the screening period, during the first cycle of efgartigimod treatment, prior to the first dose of telitacicept, and at Weeks 1, 4, 8, 12, and every 4 weeks thereafter, until the end of the study. During the screening period, prior to the first dose of telitacicept, and at Weeks 4, 12, and 24 of telitacicept treatment, BLyS/APRIL, B-cell flow cytometry, T-cell flow cytometry, and cytokines such as IL-6 will be assessed, all before dosing.

The evaluation of adverse events will adhere to the NCI-CTCAE V5.0.

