### Sample size calculation

2.7

Based on previous studies (15), the change in QMG score from baseline at 24 weeks in the monotherapy group was -9.6 (± 4.3). It is assumed that the efficacy of the two sequential treatment regimens in this study will be similar, with a predicted additional 4-point reduction in the QMG score at 30 weeks for the sequential treatment group compared to the monotherapy group (10, 19), with SD = 4.3. Using a two-sided test, α = 0.025, and power = 80%, ANCOVA will be used for pairwise comparisons, assuming R2 = 0.3. The required sample size per group is 17 participants. Considering a 15% dropout rate, 20 participants per group are planned, for a total of 60 participants.

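### Section 2.5 lets an unblinded investigator end participation, not only study drug, after discretionary rescue or perceived lack of benefit, so Week 30 QMG can be lost for outcome-related reasons and filled by LOCF

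*Protocol article*

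**What the plan says.** Section 2.5 (Criteria for discontinuing) lists when the investigator may end a patient's "participation under the following circumstances: pregnancy; receipt of rescue treatment". The list also includes the investigator's "assessment that the patient is not benefiting from the study". This is a power, not a duty, and no objective threshold is attached to lack of benefit.

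Section 2.4 uses narrower language for a myasthenic crisis: there, "investigational treatment will be immediately discontinued", and nothing is said about leaving the study. For a moderate exacerbation, such as an MG-ADL rise of at least 2 points, "the investigator may escalate standard therapy or initiate rescue treatment per clinical judgment".

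Section 2.3 says for each arm: "Participants will be followed until Week 30". Section 2.6 sets the primary endpoint as QMG change at Week 30, and its secondary endpoints, which include a QMG responder proportion, call for "assessment of the following variables at Weeks 4, 8, 12, 18, 24, and 30 after randomization". Section 2.9 names the intention-to-treat principle and fills missing primary values by last observation carried forward (LOCF). The Discussion states that the trial is not blinded.

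**The concern.** The grounds at issue, rescue and perceived lack of benefit, are both markers of poor response. The person applying them knows the arm, and outside crisis the decision to give rescue is also that person's. Two patients with the same exacerbation can therefore contribute different kinds of primary data: one an observed Week 30 QMG, the other an older score carried forward. That sits badly with the stated ITT principle.

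The direction cannot be predicted. A score from before the flare flatters the arm, and a score taken at the flare penalises it.

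A secondary endpoint is also touched, namely "the incidence of MG relapse/acute exacerbation and MG crisis at Week 30". The exacerbation that triggered rescue would normally be on record. Later events would not be, such as a crisis after that exacerbation or any event after an exit for lack of benefit.

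This is a data-collection rule. If QMG is not measured after exit, no later analysis plan can recover it.

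**Working it through.** **Reading the text.** Three features of section 2.5 suggest that participation means being in the study, not being on drug. The paragraph opens with the patient's right to withdraw from the study. Its list contains loss to follow-up and termination of the study. Section 2.4 uses a different term when only drug is meant. The Week 30 line in 2.3 is a general schedule statement, and it does not say that patients terminated under 2.5 stay in follow-up.

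**Inputs from the document.** Planned difference 4 points, SD 4.3, R² = 0.3, two-sided α = 0.025, power 80%, 17 evaluable per group, 15% dropout, 20 per group (all 2.7); QMG response threshold 3 points and the visit weeks (2.6).

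**The plan's own figure.** The adjusted SD is 4.3 × √(1 − 0.3) = 3.60. The normal approximation gives 15.4, so 16 per group. The noncentral-t version for ANCOVA has power 0.778 at 16 and 0.807 at 17, so it gives 17. Then 17 / 0.85 = 20. The sample size reproduces and is not in dispute.

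**Age of the carried-forward score at Week 30, scheduled visits only.**

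| Last QMG | Age at Week 30 |
|---|---|
| Week 24 | 30 − 24 = 6 weeks |
| Week 18 | 30 − 18 = 12 weeks |
| Week 12 | 30 − 12 = 18 weeks |
| Week 8 | 30 − 8 = 22 weeks |
| Week 4 | 30 − 4 = 26 weeks |

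**Size of a possible shift.** The gap is the difference between the carried-forward score and the Week 30 score that would have been observed. With gaps of equal size and sign:

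shift in contrast = (net number of such exits in one arm × gap) / 20

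- Equal exits and equal gaps in both arms: 0.
- One patient, 3-point gap: 3 / 20 = 0.15 points, and 0.15 / 4 = 3.75% of the planned effect.
- Planned dropout: 0.15 × 20 = 3 per arm. If all 3 in one arm and none in the other are of this kind, a 3-point gap gives 3 × 3 / 20 = 0.45 points (0.45 / 4 = 11%).
- The same split with a gap of one planned SD gives 3 × 4.3 / 20 = 0.645 points (0.645 / 4 = 16%).

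Planned standard error of the contrast: 4.3 × √0.7 × √(2/20) = 1.14. The last two cases are 0.45 / 1.14 = 0.40 and 0.645 / 1.14 = 0.57 standard errors.

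Outside the planned dropout the figure can be larger. With 25% such exits in one arm, 5% in the other and a 6-point gap, it is (0.25 − 0.05) × 6 = 1.2 points. The exit splits and the gaps are assumptions; the document gives neither.

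**The case against.** The strongest reply is that the harmful step is inferred. Section 2.5 never says that QMG assessment stops, its heading speaks only of discontinuing, and its list mixes drug-stopping grounds such as laboratory abnormalities with study exits. The article condenses a fuller protocol, which may provide for follow-up after discontinuation or an exit assessment. The sections can also be read together: rescue is allowed, exit is optional, and follow-up runs to Week 30.

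Part of this stands. The document does not show that such loss will occur, and an exit assessment would make the ages in the table wrong. But the point does not rest on a missing follow-up rule. It rests on a stated power to end participation on outcome-related grounds. At best, 2.3 and 2.5 pull in different directions, and the same amendment settles it.

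Two supporting arguments are weaker than they first look:

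- The Discussion reports score rebound 2 weeks after an efgartigimod cycle, and telitacicept's effect as significant after 4 weeks. That is a reason not to assume equal gaps across arms for early exits. However, the rebound was seen after efgartigimod alone, and the sequential regimens are timed to prevent it.
- The Discussion describes an ambitious taper with prompt rescue if symptoms worsen. That makes rescue foreseeable, but no rate is given.

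It is also fair that the illustrated shift is modest, that its upper end needs a lopsided split, and that the trial calls itself exploratory. Finally, QMG after methylprednisolone, IVIG or plasma exchange partly reflects the rescue, so how to analyse it is a choice of estimand. Collecting the data leaves that choice open, whereas ending participation can close it.

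**Conclusion.** The concern holds. As written, section 2.5 permits outcome-related and possibly arm-dependent loss of the primary measurement, which 2.9 then fills with an older value. It creates a risk, not a demonstrated bias.

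Within the planned dropout, the illustrated shift runs from 0 to about 0.65 QMG points, or up to 0.57 of the planned standard error, with unknown direction. The upper end assumes that all three planned dropouts in one arm and none in the comparator are exits of this kind, each one SD off in the same direction. This is modest but cheap to avoid, so it should be fixed. Confidence is medium, because the full protocol may already limit what ending participation means.

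**What to change.** In 2.5, make rescue and lack of benefit grounds for stopping study drug only, and add a sentence such as:

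> Participants who stop study drug or receive rescue remain in follow-up; QMG, MG-ADL, background drug doses and safety are collected to Week 30 unless consent is withdrawn.

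Section 2.9 can stay as it is. Under its ITT principle the observed Week 30 values are used, and LOCF applies only where none exists. Because QMG after rescue mixes the effect of the regimen with that of the rescue, report rescue use by arm beside the primary result.

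The cost is one amended paragraph and a few extra visits for participants off study drug. Section 3.1 reports that no one has been enrolled, so no collected data are affected. The investigator's discretion to stop study drug and the patient's right to withdraw are unchanged.
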